### Assignment of interventions

The study will comprise two arms: one intervention group (parenteral nutrition group) and one control group (oral feeding group). The Zelen single-consent design requires that consent be obtained only from the intervention group, for their participation in a study involving initiation of parenteral nutrition. The patient will be informed of the study requirements (inclusion criteria, aims, composition, expected effects and benefits, foreseeable risks, contraindications and so on) to allow them to decide whether to consent to participate. The information delivered to the patient will not mention randomization. Patients allocated to the oral feeding group will be informed about their management, and will consent only to completion of the quality-of-life questionnaire. Patients randomized to the intervention group may refuse to consent to the intervention, in which case, they will be included in the control group.

The distribution of patients between the study arms will be performed by the investigator during the first consultation to verify eligibility criteria, by means of Internet access to a 1-to-1 randomization list, balanced by center, and generated automatically by using SAS software (version 9.3; SAS Institute Inc., Cary, NC, USA) and administered by the Clinical Investigation Centre of the University Hospital of Besancon, France.

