#### Change in quality of life over time

Quality-of-life scores will be generated according to algorithms described in the EORTC scoring manual. The mechanism of missing scores will be studied and classified according to the methods of Diggle [26] and Rubin [27] (that is, MCAR (Missing Completely At Random), MAR (Missing At Random), and MNAR (Missing Not At Random). The mechanism of missing data will be determined by comparing patients with no missing scores with those with at least one missing score at baseline, according to baseline characteristics of patients. If required, more detailed patterns will be defined. If missing data are MNAR, multiple imputations may be performed. Otherwise, simple imputation by the mean will be retained.

The time to quality-of-life score deterioration (TTD) will be defined as a modality of longitudinal quality-of-life analysis and will be defined as the time from inclusion in the study to a first deterioration, with a minimum clinically significant difference of at least 5 points as compared with the baseline score, or death of any cause, whichever occurs first [28, 29]. Although three domains of the EORTC QLQ-C15-PAL are being targeted for the primary end point, scores from all domains of the questionnaire will be studied as secondary analyses. The TTD curves will be calculated by using the Kaplan-Meier method and described, by using median and 95% confidence interval (CI). TTD curves will be compared according to treatment group by using the log-rank test and univariate Hazard Ratio with 95% CI. A multivariate Cox regression model will then be performed to investigate potential prognostic factors of TTD. All variables collected at baseline will be tested by univariate analysis. Variables with a *P* value ≤0.20 by univariate analysis will be eligible for inclusion in the multivariate Cox analysis.

Mixed-model analyses of variance for repeated measures will also be performed to test a time effect, a treatment effect, and an interaction between time and treatment. If missing data are not completely at random, a pattern-mixture model will be used.

Analysis of the secondary end points will focus first on comparison of overall survival. Overall survival is defined as the time from study registration to death of any cause. Patients who are lost to follow-up will be counted at the date of their last follow-up.

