For all time-to-event end points, the 95% CI of the median survival will be calculated with the Brookmeyer and Crowley method [30]. The two treatment arms will be compared with the log-rank test.

Hazard ratios with 95% CI will be estimated by using Cox’s univariate proportional hazards model. Follow-up will be estimated by using reverse Kaplan estimation.

A multivariate Cox regression model will be performed to investigate potential prognostic factors. All variables collected at baseline will be tested in univariate analysis. Variables with an univariate *P* value ≤0.20 will be eligible for multivariate Cox analysis. A bootstrap procedure will be used to check internal validation of the model. The discriminatory capacity of the model will be assessed with Harrell C statistic. Reclassification ability will be examined with Net Reclassification Improvement (NRI) [31] and Integrated Discrimination Improvement (IDI) [32].

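### Survival and time to deterioration are compared between arms without covariates: a valid analysis, but one that gives up power which Day 1 data could recover

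*Protocol article*

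**What the plan says.** All of the time-to-event methods stand in the Protocol article under Change in quality of life over time.

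- Test, all time-to-event end points: "The two treatment arms will be compared with the log-rank test".
- Estimate: "Hazard ratios with 95% CI will be estimated by using Cox’s univariate proportional hazards model".
- TTD: "TTD curves will be compared according to treatment group by using the log-rank test and univariate Hazard Ratio with 95% CI".
- Multivariable work, survival: "A multivariate Cox regression model will be performed to investigate potential prognostic factors". TTD: "A multivariate Cox regression model will then be performed to investigate potential prognostic factors of TTD".
- Entry to those models: "All variables collected at baseline will be tested in univariate analysis", after which a variable with a P "value ≤0.20 will be eligible for multivariate Cox analysis".

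Neither multivariable model is said to keep the treatment arm or centre.

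Elsewhere, Assignment of interventions describes a "1-to-1 randomization list, balanced by center". Table 2 and the Day 1 text list WHO status, Karnofsky index, LDH, CRP, albumin, prealbumin and prior or ongoing specific treatment on Day 1 for both arms. Under Primary objective, the 2-month quality-of-life scores are adjusted for palliative chemotherapy. The change scores also take in stratification variables, centre, cancer type and patient characteristics.

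**The concern.** The trial adjusts its quality-of-life comparisons but drops all adjustment for survival and TTD, and gives no reason. Eligibility spans mixed solid tumours, with curative-type treatment either stopped or still running, so a wide spread in prognosis is plausible. In a Cox or log-rank comparison, leaving out a strong prognostic factor lowers the power for the treatment effect.

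This matters because overall survival is the first secondary comparison, and because Hypotheses and objectives asks for better quality of life with survival not significantly worse. Under that wording, a weaker test makes it easier to conclude that survival was not harmed. The sample size is set on quality of life alone; no event count or power is given for survival.

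**Working it through.** **Plan's own figure.** There is none to reproduce: the document states no event count, hazard ratio or power for survival or TTD. From the document I take only N = 140, 1:1 allocation balanced by centre, and 10 centres (Sample size and recruitment). All other inputs below are assumptions.

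**Step 1: power before any loss.** Schoenfeld's formula at two-sided 5% is power = Φ(|ln HR| × √d / 2 − 1.96). With an assumed HR of 0.62, |ln HR| = 0.478.

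- d = 100 deaths: 0.478 × 5.000 − 1.96 = 0.43, power 67%
- d = 120: 0.478 × 5.477 − 1.96 = 0.66, power 75%
- d = 140: 0.478 × 5.916 − 1.96 = 0.87, power 81%

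Power is limited even if almost everyone dies during follow-up.

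**Step 2: loss from omitting a prognostic score.** Simulation settings: 140 patients, 10 centres of 14, conditional HR 0.62, exponential survival with a control median of 4 months at an average score, censoring uniform over 6 to 30 months, and one standardised Day 1 score with log hazard ratio g per SD. There were 1,000 trials per setting, so the Monte Carlo standard error is at most about 1.6 points. With no centre effect:

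| g | Power, unadjusted | Power, adjusted | Loss (points) | Mean HR, unadjusted | Mean HR, adjusted |
|---|---|---|---|---|---|
| 0 | 72.6% | 72.9% | 0 | 0.62 | 0.62 |
| 0.4 | 67.5% | 74.1% | 7 | 0.64 | 0.61 |
| 0.7 | 52.5% | 71.6% | 19 | 0.69 | 0.62 |
| 1.0 | 41.5% | 69.9% | 28 | 0.72 | 0.62 |

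With a centre effect of SD 0.3 on the log-hazard scale, the losses for g = 0.4, 0.7 and 1.0 are 6, 18 and 29 points (59.5% vs 65.2%, 49.0% vs 67.1%, 38.9% vs 67.5%).

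**Step 3: the harmful direction.** A separate simulation used a true HR of 1.5, median survival 90 days, censoring uniform over 180 to 900 days, 120 to 132 deaths, three covariates and 600 trials per setting. For a prognostic index SD of 0.5, 0.8 and 1.0, unadjusted power was 52%, 34% and 31%, against 62%, 61% and 62% adjusted. The losses are 10, 27 and 31 points. The mean unadjusted HR was 1.42, 1.33 and 1.30.

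**Step 4: validity.** With HR = 1, the unadjusted analysis rejected in 4.1% to 5.8% of trials in the first simulation and 3.8% in the second. Type I error is not inflated.

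**Step 5: centre.** Full stratification by 10 centres, on top of the score at g = 0.7, lowered power from 72% to 64% with no centre effect and from 67% to 63% with a centre SD of 0.3. The gain comes from the prognostic covariates, not from centre strata.

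**The case against.** The strongest reply is that an unadjusted log-rank test with a univariate Cox hazard ratio is a standard, fully specified intention-to-treat comparison of a secondary end point, so only efficiency is at issue. That stands. Several further points on that side also stand and set the limits of this one.

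- A reader might infer that the unadjusted hazard ratio is biased and hides a survival harm. The documents do not support this. The Cox hazard ratio is non-collapsible: the unadjusted model estimates a marginal ratio and the adjusted model a conditional one, and they differ even under perfect randomization. Much of the shift in Steps 2 and 3 is this difference. The power loss is the real cost.
- A reader might infer that deaths will be few. Follow-up runs until death, and the second simulation has 120 to 132 deaths among 140 patients. Limited power is the accurate description.
- A reader might infer that the P ≤ 0.20 model is an invalid treatment-effect model. The document offers it only as a search for prognostic factors, with bootstrap, C statistic, NRI and IDI. It simply does not fill the gap.
- A reader might infer that balancing by centre obliges a centre-stratified analysis. Step 5 shows that this can cost power here.
- The superiority rule under Primary objective has no survival criterion; survival enters through the aims. This lowers the stakes without removing them.
- Day 1 follows randomization, and the patient has by then received the arm-specific leaflet. WHO and Karnofsky status are thus rated with allocation known, and a randomized patient who never reaches Day 1 has no covariate values.
- Both simulations adjust for the true prognostic variables in the right form, which is a best case. Eligibility may also narrow the prognostic spread.

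The promise of a formal analysis plan before database lock does not dispose of the matter, because this document already fixes the comparison as unadjusted.

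**Conclusion.** The point holds as one of efficiency. The survival and TTD comparisons are valid as written, but they leave unused Day 1 information that the trial collects in both arms and that it partly uses for quality of life. The cost is about 6 to 29 points of power in one set of assumptions and 10 to 31 in the other. It is nil if the Day 1 values carry no prognostic information, in which case adjusting for one pre-named score also lost nothing. The range rests on assumed hazard ratios, survival times and prognostic strengths, none of which the document gives. Adjustment would not make survival well powered: the adjusted analyses still reach only about 62% to 74% at the assumed effects. The change is worth making, but nothing here invalidates the planned test.

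**What to change.** Pre-specify, before database lock, one Cox model for overall survival and one for TTD:

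1. Force the treatment arm in, with patients analysed as randomized.
2. Fix a short covariate list less open to knowledge of allocation, for example log CRP, albumin and palliative chemotherapy at Day 1. Leave out WHO and Karnofsky status, or confine them to a sensitivity analysis.
3. Handle centre with a method suited to about 14 patients per centre (140 / 10), such as a shared frailty term, rather than full stratification. The frailty option was not simulated here.
4. State how missing Day 1 values are handled, so that every randomized patient stays in the model.
5. Report this model alongside the unadjusted log-rank test and hazard ratio, and label the adjusted ratio as conditional.
6. Keep the P ≤ 0.20 model, labelled as exploratory prognostic work.

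The cost is a few lines of analysis text and no new data. The downsides are small: some missing laboratory values to handle, and two hazard ratios with different meanings to explain.

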### Ethics

#### Research ethics approval

This protocol is governed by French legislation concerning interventional biomedical research and, as such, was submitted to the local ethics committee (Comité de Protection des Personnes Est II) and approved on January 23, 2012, under the number 11/623. The study was also approved by the French Health Products Safety Agency (Agence Nationale de Sécurité du Médicament et des produits de santé, ANSM) on May 14, 2012. The database was registered with the French national authority for the protection of privacy and personal data (Commission Nationale de l’Informatique et des Libertés, CNIL). Computerised data are processed anonymously. An anonymous identification code will be attributed to each participating in the study, and the list identifying participating patients with their personal data will be stored by the investigator and kept strictly confidential and will not be disclosed to the study sponsor.

To offset any potential remarks on the ethical issues raised by the use of the Zelen design, we came to an agreement with the President of the Ethics Committee that approved the study that we would also consult the Institutional Review Board of the University Hospital of Besancon, as well as a local group of patient associations to obtain their opinion on the choice of randomization method. The study synopsis, a short note explaining the specificities of the Zelen design (accompanied by a figure), and the patient information leaflets from the study were provided. The study was examined by the Institutional Review Board who gave their approval, indicating that the study appeared to protect the patients and was likely the only means to perform a study of this type.

#### Information and consent

Information will be given to all patients on the day of the first consultation. Informed-consent forms will be signed by both the patient and the investigator, with a copy for each, and the original stored by the investigator. Participants are informed in the patient-information leaflet that the data generated by the study will be conserved in electronic format for 15 years. In particular, it is noted that individual data relating to them will be accessible only to the investigator, or to the relevant health authorities for official inspection or a quality audit by official representatives appointed by the sponsor.

Contrary to the classic randomization procedure for clinical trials, the Zelen design proposes that randomization be performed before patients give their consent to participate. The patient information therefore contains no mention of the randomization procedure to minimize the difficulty of obtaining informed consent, thus increasing participation. Once randomization has been performed, patients assigned to the intervention group are then approached for consent (single-consent design). In this design, the patient information and informed consent discuss only the modalities related to the intervention (that is, parenteral nutrition) inclusion criteria, objectives, composition, expected effects, foreseeable risks and benefits, contraindications, administrative issues, follow-up. However, in the ALIM-K study, the patients in both groups will give consent for completion of the quality-of-life questionnaire.

## Discussion

A well-designed, randomized, controlled study comparing parenteral nutrition with oral feeding is needed to reach a consensus on the best form of nutrition in malnourished patients at the palliative phase of advanced cancer. Studies of this type have previously been performed in many patient populations, including patients with cancer [33–37], but with only a very few studies in patients at the palliative phase [12]. This latter study highlights the difficulty of performing randomized controlled trials in palliative care, because the inclusion of the sample size of 309 patients took 6 years.

Performing randomized clinical trials on nutrition in patients at the palliative stage of advanced cancer, a particularly vulnerable population, remains a challenge. It requires the ultimate respect for the patients, many of whom are totally opposed to the idea of any kind of research at this stage of their life and illness. Indeed, being too ill was the most frequently cited motive for refusal to participate in a randomized study by Rabow *et al*. [38] comparing the efficacy of palliative care with standard management in outpatient care for patients with advanced congestive heart failure, chronic obstructive pulmonary disease, or cancer. It is often difficult for patients and their families to accept the idea that research would still be possible at this stage of their illness, let alone the idea that random allocation might be the best option, given the medical uncertainty surrounding the efficacy of the mode of nutrition to be administered. Furthermore, randomization for patients in this context can appear to the patient to “dehumanize” the relation with caregivers and the healthcare system, which can justifiably cause considerable worry and anxiety in the face of the medical community’s uncertainty.

To avoid the possible information bias mentioned and its associated deleterious effects on participation rates, we decided to use the Zelen single-consent design for the ALIM-K study. This choice was approved by the Ethics Committee, the Institutional Review Board, and a group representing patient associations. Many experts initially considered the Zelen method to be a violation of the ethos, if not the very letter of the law, regarding informed consent [39]. However, the method was found to be attractive for research in situations of great precariousness and is used in a variety of different contexts [40]. Patients remain free to express their preference for another treatment approach at any time.

Nonetheless, recruitment remains challenging for several reasons. The methodology of the Zelen design used in the ALIM-K study provides an opportunity to investigate the factors that influence the decision by patients or physicians to accept (or not) artificial nutrition in the setting of palliative care for advanced care. At the palliative stage of cancer, the main end point is quality of life, even though this term may appear to be a misnomer to many patients at the end of life. The QLQ-C15 PAL questionnaire used in our study presents the advantage of addressing simple issues related to daily life, and is quick and easy to complete.

Because our randomization procedure takes into consideration the fragility of this patient population, and the design is close to the reality of routine practice, it will be interesting to see which factors emerge as predictors of refusal or acceptance of artificial nutrition.

## Trial status

Between May 2012, and April 2013, 13 patients were included in two centers to check the feasibility and understanding of the questionnaires, as well as their acceptability. Qualitative analyses of these pretest data confirmed that methods and questionnaires are acceptable and that the study is feasible. The main adjustment to result from this test phase was greater precision required in some of the inclusion criteria.

At the time of submission of the manuscript, the ALIM-K study is ongoing. All 10 centers were enrolling progressively, and the last participating center (Lille) was opened on April 16, 2014. Patient recruitment is not complete, at the time of submission.

## Abbreviations

ANOVA: analysis of variance
ANSM: Agence Nationale de Sécurité du Médicament et des produits de santé (French Agency for the Safety of Health Products)
BMI: body mass index
CI: confidence interval
CNIL: Commission Nationale de l’Informatique et des Libertés (French National Authority for the Protection of Privacy and Personal Data)
CRP: C-reactive protein
EORTC: European Organisation for Research and Treatment of Cancer
ESPEN: European Society for Parenteral and Enteral Nutrition
IDI: Integrated Discrimination Improvement method
IRB: institutional review board
MAR: missing at random
MCAR: missing completely at random
MNAR: missing not at random
NRI: Net Reclassification Improvement method
QLQ-C15 PAL: Quality of Life Questionnaire Core 15 Palliative
QLQ-C30: Quality of Life Questionnaire Core 30
QUAL-E: Questionnaire of Quality of Life at End of Life
SD: standard deviation
SFNEP: Société Francophone Nutrition Clinique et Métabolisme
TTD: time to quality of life score deterioration.
